### Sample size justification

2.4

Sample size for this randomized, sham-controlled pilot and feasibility trial was determined in full alignment with the CONSORT 2010 Statement: Extension to Randomized Pilot and Feasibility Trials (Eldridge et al., 2016), and the optimized sample size estimation method for pilot trials with continuous primary outcomes established by Whitehead et al (Whitehead et al., 2016). As an external pilot trial, the core aim of sample size setting is not to power formal hypothesis testing for intervention efficacy, but to generate a sufficiently precise estimate of the standard deviation of our primary outcome (Metformin Symptom Severity Score total score) to inform the design of a future definitive randomized controlled trial. In detail, according to the optimized sample size estimation method for pilot trials established by Whitehead et al., an estimated final sample of 25 evaluable participants per group (after accounting for a 15% attrition rate from the 30 enrolled participants) yields 48 degrees of freedom for variance estimation. This well exceeds the minimum threshold of 20 degrees of freedom recommended in the literature for stable, unbiased variance estimation in pilot research. No formal hypothesis testing for intervention efficacy is planned in this pilot trial. Core feasibility endpoints include: recruitment rate (target ≥8 participants per month), screening failure rate, treatment adherence rate (defined as completing ≥80% of scheduled treatment sessions), attrition rate (estimated at 15% based on published neuromodulation trials in patients with T2DM), and protocol violation rate. Accounting for a 15% attrition rate, the final enrollment target is 60 participants (30 per group) (Whitehead et al., 2016).

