### Randomization and blinding

2.5

Participants will be randomized 1:1 to taVNS group or sham control group, with stratification by age and gender to balance baseline characteristics between groups. The randomization sequence will be generated by an independent third-party biostatistician using SPSS 26.0, with group allocation sealed in sequentially numbered, opaque envelopes for strict allocation concealment. After baseline assessment, a dedicated study coordinator (fully blinded to group assignment) will open envelopes in numerical order to assign eligible participants.

Given the anatomical specificity of active and sham stimulation sites, intervention staff responsible for electrode placement and device operation cannot be blinded to group allocation. To mitigate potential bias, we have implemented pre-specified rigorous safeguards: The blinded coordinator exclusively manages group allocation, and only provides intervention staff with pre-marked anatomical diagrams of stimulation sites, with no disclosure of group identity at any time. Non-blinded intervention staff are strictly barred from outcome assessment, data entry, statistical analysis, or any communication with participants about group allocation or expected intervention effects. Both groups use identical stimulators with consistent nominal parameters; all intervention staff receive centralized standardized training to ensure identical operational execution and participant interaction across groups.

All outcome assessors, data analysts, biostatisticians, and participants will remain fully blinded to group allocation throughout the trial. Furthermore, treating physicians are solely responsible for routine clinical management and safety assessments; they have no access to group allocation and are strictly isolated from intervention implementation and outcome assessment. Participants will be informed that both interventions may induce a mild tingling sensation, and subjective feeling cannot be used to infer group assignment, to minimize anticipation bias. Outcome assessors will receive standardized training and regular inter-rater reliability checks to reduce measurement bias.

The effectiveness of the blinding will be formally assessed in Weeks 2 and 4 using the validated James Blinding Index (BI) method (James et al., 1996). The detailed statistical procedures for this assessment are outlined in the “Statistical Methods” section.

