Complete case analysis will be conducted as a sensitivity analysis to verify the robustness of the core findings. Exploratory subgroup analyses stratified by age, sex, and diabetes duration are descriptive only.

The success of blinding will be evaluated using the James BI for all participants and independent outcome assessors at Week 2 and Week 4. The BI is scaled from 0 (all participants guessed correctly) to 1 (all participants guessed incorrectly), with 0.5 indicating completely random guesses (the standard for successful blinding). Weights are assigned consistent with the original James method: 0.00 for correct guesses, 1.00 for incorrect guesses, and 0.50 for uncertain/unable to judge responses, with uncertain responses split equally between correct and incorrect guesses. The BI and its 95% CI will be calculated using the jack-knife procedure recommended in the original method (James et al., 1996).

Safety parameters (CBC, ALT, AST, urea, creatinine) are analyzed similarly, comparing abnormality rates. All tests are two-sided with α = 0.05; effect sizes are reported with 95% CI.

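### Only one blinding index is named and none by arm, so 0.5 does not by itself establish random guessing and a lower value cannot show which arm was unblinded

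*Protocol article*

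**What the plan says.** Section 2.5 (Randomization and blinding) announces a formal assessment of blinding at Weeks 2 and 4 and refers to section 2.10 for the procedure. Section 2.10 (Statistical methods) then fixes it:

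- Respondents and times: "The success of blinding will be evaluated using the James BI for all participants and independent outcome assessors at Week 2 and Week 4".
- End points of the scale: "The BI is scaled from 0 (all participants guessed correctly) to 1 (all participants guessed incorrectly").
- Mid-point, which serves as the criterion of success: "with 0.5 indicating completely random guesses (the standard for successful blinding").
- Weights: "0.00 for correct guesses, 1.00 for incorrect guesses, and 0.50 for uncertain/unable to judge responses".
- Interval: "The BI and its 95% CI will be calculated using the jack-knife procedure recommended in the original method".

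Neither section mentions an index by arm or a table of guesses by arm. The text does not use the word pooled. That one figure covers both arms is the natural reading of an index defined for all participants.

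**The concern.** A single figure over both arms sums up two separate questions: do participants on taVNS know they have it, and do participants on sham know they have sham? Opposite answers cancel, and the same total can come from either arm. The 0.5 standard can then be met by guessing that is far from random, and a shortfall below 0.5 cannot be traced to an arm.

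This matters more here than in many trials:

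- The primary outcome is self-reported (section 2.7.2), so belief about allocation can act on it directly.
- All participants are told that both interventions may cause tingling (section 2.5). A shared leaning to active is therefore plausible.
- The intended difference between arms is the ear site (section 2.6.3), and after three supervised sessions participants may treat themselves at home (section 2.6.4). Recognition of the sham site in one arm is a realistic possibility.
- The pilot exists to inform a definitive trial (section 2.4). Whether the sham was recognised as a sham bears on whether it can be used again.

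**Working it through.** **Inputs.** Weights of 0 (correct), 1 (incorrect) and 0.5 (uncertain) come from section 2.10. Section 2.4 gives 1:1 allocation, "the final enrollment target is 60 participants (30 per group"), and 25 evaluable per group. The guessing patterns below are illustrative assumptions.

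**Formula (assumed).** The article prints weights but no formula. Taking the index as the mean weight, BI = P(incorrect) + 0.5 × P(uncertain).

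**The plan's own anchors.** With 60 guesses: all correct gives 0/60 = 0; 30 correct and 30 incorrect gives 30/60 = 0.5; all incorrect gives 60/60 = 1. All three stated anchors reproduce.

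**Link to the arms.** Let d be an arm's P(correct) − P(incorrect). Each arm's BI is 0.5 − d/2. With equal arms A (taVNS) and S (sham), the pooled BI is 0.5 − (dA + dS)/4. Only the sum of the two d values matters.

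**Case 1: the same share of both arms guesses active, nobody uncertain.** A guess of active is correct on taVNS and incorrect on sham, so dS = −dA and the pooled BI is 0.5 whatever the share. Delete-one jack-knife intervals at 30 per arm:

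| Share guessing active | taVNS BI | Sham BI | Pooled BI (95% CI) |
|---|---|---|---|
| 50% | 0.50 | 0.50 | 0.50 (0.37 to 0.63) |
| 70% | 0.30 | 0.70 | 0.50 (0.37 to 0.63) |
| 80% | 0.20 | 0.80 | 0.50 (0.37 to 0.63) |
| 100% | 0.00 | 1.00 | 0.50 (0.37 to 0.63) |

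In the 80% row the arm intervals are 0.05 to 0.35 and 0.65 to 0.95. At 25 per arm they are 0.04 to 0.36 and 0.64 to 0.96, and the pooled interval is 0.36 to 0.64.

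**Case 2: one arm 80% correct, the other at random.** The 80% arm has BI 0.20 and the other 0.50, so the pooled BI is (0.20 + 0.50)/2 = 0.35. The sum is symmetric, so the result is the same whichever arm was unblinded. At 30 per arm the 95% CI is 0.23 to 0.47. It excludes 0.5: the failure is detected but not located.

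**Precision of arm-level values.** With no uncertain answers, SE(d) = √((1 − d²)/n). At n = 25:

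- d = 0.60: √(0.64/25) = 0.16, and 0.60 ± 1.96 × 0.16 gives 0.29 to 0.91.
- d = 0: √(1/25) = 0.20, and ± 1.96 × 0.20 gives −0.39 to 0.39.

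**The case against.** **The anchor is right.** Random guessing does give 0.5, and the pooled index does detect failure in Case 2. If everyone in both arms guesses active, the guesses carry no information about allocation, so reading 0.5 as blinding preserved is defensible there. This stands. The sentence on 0.5 needs a qualifier, not deletion, and the index remains a valid overall summary.

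**Arm-level values have their own ambiguity.** If all participants guess active, dA = +1 and dS = −1 although nobody can tell the arms apart. An arm's d mixes a general leaning with true recognition. This also stands, so the two arms have to be read together with the table of guesses.

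**It is an enhancement.** The plan already specifies a published index with weights, times and interval method. That is fair, and it limits the weight of the point. It does not remove the gap in what the index can show.

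**A stronger reading that the documents do not support.** A reader might infer that the jack-knife interval for the outcome assessors is too narrow, because a few assessors each guess for many participants. The article does not give the number of assessors, the guesses per assessor or the unit deleted in the jack-knife. The mention of "regular inter-rater reliability checks" shows at most that there is more than one assessor. The narrowing is also conditional. In simulation with 60 guesses deleted one at a time and 2, 3 or 5 assessors, a mere habit of answering active, with both arms mixed within each assessor, left coverage at 94% to 96%. Coverage fell only when assessors differed in accuracy: at an assumed intraclass correlation of 0.05 it was 78%, 83% and 88%.

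**Conclusion.** The point holds in limited form. With one index and none by arm, 0.5 is compatible with random guessing but does not by itself establish it. A value such as 0.35 signals unblinding without showing whether the taVNS or the sham arm is responsible. In the 80% example, arm values of 0.20 and 0.80 are hidden behind a pooled 0.50.

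This rests on two assumptions: that the index is the mean of the stated weights, and that one figure is computed over both arms. The guessing shares are illustrations, not predictions.

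The point concerns only how blinding is described. It does not show that blinding will fail, that the James index is wrong, or that any efficacy or sample-size result is affected. Nor can it be said that the assessor interval is too narrow. It is a cheap improvement of low severity.

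**What to change.** In section 2.10, using the guesses already to be collected at Weeks 2 and 4:

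1. Keep the James index as the overall summary. Add an arm-specific blinding index (Bang) with 95% CI for each arm and visit.
2. Report the 2x3 table at each visit: arm by guess (active, sham, uncertain).
3. State that the two arms are interpreted together, because a shared leaning to active also shifts the arm values in opposite directions.
4. Qualify the standard, for example: *a value of 0.5 is expected under random guessing but does not by itself establish it; the arm-level results are needed to interpret it.*
5. Report assessor guesses separately from participant guesses. If each assessor judges many participants, state whether the jack-knife deletes guesses or assessors.

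The cost is a few lines of text and one table, with no new data. The downside is imprecision: the arm-level intervals are as wide as shown for 25 per arm, so they should be presented as estimates and not as a pass or fail test.

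### The blinding score defined in section 2.10 is not the James index it is named after, because it gives 'don't know' answers a weight of 0.50 where James gives them the top weight of 1

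*Protocol article*

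**What the plan says.** Section 2.5 (Randomization and blinding) states that blinding will be formally assessed at Weeks 2 and 4 "using the validated James Blinding Index (BI) method" and refers to the statistical section for details. Section 2.10 (Statistical methods) then fixes the following:

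- **Who is assessed:** blinding is "evaluated using the James BI for all participants and independent outcome assessors at Week 2 and Week 4".
- **Ends of the scale:** "The BI is scaled from 0 (all participants guessed correctly) to 1 (all participants guessed incorrectly").
- **Midpoint and benchmark:** the same sentence goes on "with 0.5 indicating completely random guesses (the standard for successful blinding").
- **Source of the weights:** "Weights are assigned consistent with the original James method".
- **Weights:** "0.00 for correct guesses, 1.00 for incorrect guesses, and 0.50 for uncertain/unable to judge responses".
- **Unsure answers:** the rule is then restated, "with uncertain responses split equally between correct and incorrect guesses".
- **Interval:** "The BI and its 95% CI will be calculated using the jack-knife procedure".

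These are positive statements of the rule. They are not details left to another document.

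**The concern.** The James index is built around 'don't know' answers. It treats them as the strongest evidence of blinding and gives them the highest weight, so a sample in which everyone is unsure scores 1. Section 2.10 treats the same answers as coin-flips, so that sample scores 0.5. The protocol therefore names one index and defines another, and an analyst cannot follow both.

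The difference depends wholly on uncertain answers, and this trial may well collect many. Under section 2.5, participants are told that both interventions may tingle and that sensation cannot be used to infer the group. The result will also be looked at closely: the primary outcome is self-reported (2.7.2), most sessions may be done at home (2.6.4), intervention staff are not blinded (2.5), and the Discussion lists expectation bias as a limitation. A mislabelled index could mislead a judgement about the sham for the later definitive trial. It could not be compared with James indices reported elsewhere.

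**Working it through.** **Inputs.** The weights, scale and jack-knife interval come from section 2.10. The 25 evaluable participants per group come from section 2.4 and the 1:1 allocation from section 2.5. The guess tables are assumptions, because the article gives no expected distribution of answers.

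**Score as written:** S = P(incorrect) + 0.5·P(uncertain).

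**James index (standard definition):** BI = [1 + P_DK + (1 − P_DK)·K_D]/2, with K_D = (P_Do − P_De)/P_De. P_Do and P_De are the observed and chance-expected weighted disagreement among those who guess. The weights are 0 for correct, 0.5 for incorrect and 1 for don't know.

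**Step 1: the protocol's own anchors.** With nobody unsure and equal arms with symmetric guesses, K_D = 2·P(incorrect) − 1.

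- All correct: S = 0; BI = (1 − 1)/2 = 0.
- All incorrect: S = 1; BI = (1 + 1)/2 = 1.
- Even split: S = 0.5; BI = (1 + 0)/2 = 0.5.

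Both rules reproduce 0, 1 and 0.5, so the anchors are correct when nobody is unsure.

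**Step 2: the weight for incorrect guesses.** With two arms this weight multiplies both P_Do and P_De, so it cancels in K_D. Printing 1.00 where James has 0.50 changes nothing.

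**Step 3: the weight for unsure answers.** With equal arms and symmetric guesses, K_D = 2·P(incorrect)/(1 − P_DK) − 1. Substituting,

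BI = [1 + P_DK + 2·P(incorrect) − (1 − P_DK)]/2 = P_DK + P(incorrect).

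Hence BI − S = P_DK/2, half the share of uncertain answers.

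**Step 4: worked example, 15 unsure / 8 correct / 2 incorrect per arm (n = 50).**

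- As written: 4/50 + 0.5 × 30/50 = 0.08 + 0.30 = 0.38.
- James: P_DK = 30/50 = 0.6; P_Do = 0.5 × 4/20 = 0.10; P_De = 0.5 × 0.5 = 0.25; K_D = (0.10 − 0.25)/0.25 = −0.6; BI = [1 + 0.6 + 0.4 × (−0.6)]/2 = 0.68.
- Gap: 0.68 − 0.38 = 0.30 = 0.6/2.

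**Step 5: other tables, with leave-one-out jack-knife 95% CIs.**

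| Per arm: unsure / correct / incorrect | As written | James |
|---|---|---|
| 25 / 0 / 0 | 0.50 | 1.00 |
| 12 / 9 / 4 | 0.40 (0.303 to 0.497) | 0.64 (0.503 to 0.777) |
| 15 / 8 / 2 | 0.38 (0.298 to 0.462) | 0.68 (0.548 to 0.812) |
| 20 / 5 / 0 | 0.40 (0.344 to 0.456) | 0.80 (0.688 to 0.912) |

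In the last three rows the two intervals lie wholly on opposite sides of 0.5.

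**Step 6: the reverse misreading.** In the 20/5/0 row nobody guesses incorrectly. If a standard routine returns the James value of 0.80, the printed scale, whose only upper anchor is all guesses incorrect, suggests predominantly wrong guessing.

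**Step 7: how often the intervals disagree.** There are 27 × 26/2 = 351 symmetric tables with 25 per arm, or 350 without the all-unsure one. In 20 of these the written interval lies wholly below 0.5 and the James interval wholly above it. They run from 12/9/4 to 23/2/0.

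**The case against.** A reader might infer more than the article supports, and most of the reply to those stronger readings stands.

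- **That adequate blinding will be reported as failed.** The 20 discordant tables all need at least 12 of 25 unsure per arm and at least 69% (9/13) of guessers correct. The 12/9/4 table is a near miss: moving one person per arm from correct to incorrect (12/8/5) gives 0.44 (0.34 to 0.54) as written, no longer wholly below 0.5. Section 2.10 names 0.5 as its standard but does not say that an interval below it means failure. Whether lopsided guessing among a minority counts as adequate blinding is also a choice of method, and the written score is arguably the more cautious one. If everyone is unsure, or guessers split evenly, the written score is 0.5 and meets the protocol's standard.
- **That the 0, 0.5 and 1 anchors are wrong.** They hold when nobody is unsure. What is missing is that complete uncertainty also scores 1.
- **That uncertain answers are handled in two conflicting ways.** A weight of 0.50 and an equal split between 0 and 1 are the same rule.
- **That efficacy results are at risk.** No endpoint or model uses the index, and section 2.4 does not list blinding among the core feasibility endpoints.

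The cited source is not available here, so the point rests on the standard definition of a named statistical method. None of this rescues the attribution: the stated weight for unsure answers does not belong to the index that the protocol names.

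**Conclusion.** The point holds as an error of definition and labelling in a rule that the protocol states outright. The score in section 2.10 differs from the James index in one effective element, the weight for uncertain answers. The shortfall is half the share of uncertain answers, given equal arms and symmetric guesses: nil if nobody is unsure and 0.50 if everybody is. With many uncertain answers and mostly correct guesses among the rest, the two can fall on opposite sides of 0.5. How likely that is cannot be judged from the article, because it gives no expected guess distribution. The consequence is confined to the blinding assessment. The primary outcome analysis and the sample size are unaffected.

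**What to change.** Choose one of two corrections in section 2.10:

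1. Keep the James index. Compute it by its defining formula with a weight of 1 for don't know, and add to the scale that complete uncertainty also scores 1, so that a high value is not read as wrong guessing alone.
2. Keep the stated weights. Remove the James name and the claim that the weights follow that method, here and in section 2.5, and describe the score as the proportion incorrect plus half the proportion uncertain.

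In either case report the table of guesses by arm (correct, incorrect, unsure) at Weeks 2 and 4, so that readers can calculate either index. The cost is about two sentences and, for the first option, a standard software routine. No new data are needed.

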#### Exclusion criteria

2.3.4

Subjects meeting any of the following will be excluded:

(1) Acute or chronic diarrhea attributable to confirmed gastrointestinal pathology or systemic disease (including but not limited to hepatic, biliary or pancreatic disease; infectious diarrhoeal illnesses such as dysentery or cholera; systemic diseases, intoxications, parasitic infections; malignancy; prior gastric bypass surgery);(2) Severe cardiovascular or cerebrovascular disease, diabetic ketoacidosis, or other serious endocrine, haematologic or psychiatric disorders likely to affect compliance or follow-up;(3) Use of antibiotics, proton pump inhibitors, H_2_-receptor antagonists, probiotics/prebiotics or other agents known to substantially alter the gut microbiota within 4 weeks prior to enrollment;(4) Pregnancy, planned pregnancy, or lactation;(5) Marked glycaemic instability;(6) Current insulin therapy;(7) Severe skin lesions in the auricular concha or absence/deformity of the auricle that precludes intervention;(8) Fear of the intervention or inability to tolerate conventional electrical stimulation;(9) Known allergy or contraindication to metformin hydrochloride;(10) Participation in another clinical trial or any condition likely to prevent completion of the study follow-up.

Note: any participant who meets one or more of the exclusion criteria above will be ineligible for enrollment.

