#### Standard care (background therapy)

2.6.1

Background therapy follows international guideline recommendations and comprises standardized lifestyle counseling and medication management. Lifestyle counseling includes: dietary guidance with carbohydrates accounting for 45–60% of total daily energy intake and dietary fiber ≥25 g/day; at least 150 min/week of moderate-intensity aerobic activity (for example, brisk walking or cycling); and standardized education on disease management, medication adherence, and management of gastrointestinal symptoms to ensure consistency across participants (American Diabetes Association, 2024a,b).

Medication management principles are as follows:

Discontinue or avoid medications known to exacerbate gastrointestinal symptoms where clinically appropriate (e.g., stimulant laxatives or certain over-the-counter preparations);

In participants with inadequate glycaemic control, additional antihyperglycaemic agents (for example, SGLT2 inhibitors or DPP-4 inhibitors) may be added as clinically indicated, provided such additions are unlikely to aggravate gastrointestinal function; adjustments will follow current guideline recommendations and be documented;

Concomitant treatment for chronic conditions (e.g., antihypertensives for hypertension or secondary prevention therapies for coronary artery disease) will be maintained but clinicians should avoid introducing agents known to provoke GI intolerance when alternatives are available.

Metformin dosing will follow a “start low, escalate gradually” regimen: initial dose 500 mg administered with meals twice daily; dose titration will proceed weekly guided by fasting blood glucose (target 4.4–7.0 mmol/L), with a maximum dose up to 2,000 mg/day or the participant's maximal tolerated dose. Dose adjustments and all concomitant medications will be supervised and recorded by study physicians. In the event of severe, poorly tolerated diarrhea (e.g., ≥5 bowel motions per day with clinical signs of dehydration), metformin will be withheld or adjusted and symptomatic therapy provided (e.g., diosmectite); severe events will be managed according to the study Serious Adverse Event (SAE)—defined per the Common Terminology Criteria for Adverse Events (CTCAE) as any adverse event resulting in death, life-threatening illness, hospitalization, persistent disability, or requiring immediate emergency intervention—procedure and continue to be followed up (Rena et al., 2013).

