#### Observation schedule and sample handling

2.6.5

The overall observation period is 5 weeks, comprising a 1-week baseline period (Week −1 to 0), a 2-week treatment period (Weeks 0–2), and a 2-week follow-up period (Weeks 2–4). Primary and key secondary outcomes (Metformin Symptom Severity Score, Bristol Stool Form Scale, and bowel urgency) as well as glycaemic/metabolic indices and selected inflammatory and mechanistic biomarkers will be assessed at baseline, Week 2, and Week 4. Selected biochemical markers will be repeated at baseline and either Week 2 or Week 4 according to the prespecified sampling schedule in the protocol appendix.

All biological specimen collection, processing, transport, and storage will follow a unified SOP. Blood samples will be drawn after an overnight fast unless otherwise specified, kept short-term at 4 °C, and transferred to long-term storage at −80 °C within the time limits defined in the SOP. Laboratory assay methods, quality-control procedures, and batch management are described in the trial appendix. The timeline of interventions, assessments, and visit windows is detailed in Table 1; adverse-event monitoring will be continuous throughout the entire study period.

**Table 1 T1:** Treatment and data collection.

Category	Study phase	Baseline	Visit 1	Visit 2
	Visit window	(Day 0)	Week 2	Week 4
Information collection	Basic medical history collection	×		
	Informed consent obtained	×		
	General demographics collection	×		
	Past medical and treatment history	×		
	Comorbidities and treatment history	×		
	Eligibility criteria check	×		
Primary outcomes	Metformin symptom severity score	×	×	×
Secondary outcomes	Bristol stool form scale	×	×	×
	Defecation urgency	×	×	×
	Quality of life scale	×	×	×
	FBG	×	×	×
	PG2h	×	×	×
	GA	×	×	
	IL-6, IL-10, TNF-α		×	
	GLP-1, BA, 5-HT, D-LA		×	
	ALT, AST, BUN, Cr (liver and renal function)		×	
Sample and data management	Adverse events (AEs) monitoring		×	×
	Sample collection record		×	
	CRF review by investigator (CRF-PI)	×	×	×
	CRF review by monitor (CRF-MON)	×	×	×
	Blinding assessment		×	×

“ × ” indicates that the corresponding assessment is performed at that visit. Baseline = day 0; visit 1 = week 2 (±3 days); visit 2 = week 4 (±3 days). All blood and stool specimens will be collected after an overnight fast.

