#### Safety assessments

2.7.4

Safety evaluations include complete blood count, liver function (ALT, AST), and renal function (urea, creatinine). Assessment at baseline and Week 2.

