### Safety evaluation

2.9

All AEs will be graded and analyzed according to standardized systems. For practical purposes, a simplified grading mapped to the CTCAE is applied as follows:

Grade 1 (Mild): Minor symptoms requiring no intervention or only simple supportive care.

Grade 2 (Moderate): Requires outpatient management or limitation of daily activities.

Grade 3 (Severe): Requires hospitalization or prolongation of hospitalization.

Grade 4 (Life-threatening): Requires emergency intervention or life support.

Grade 5: Death directly related to the AE.

Safety endpoints include incidence, severity distribution, onset timing, intervention-related causality of AE/SAE, and laboratory abnormalities (CBC, liver and renal function). Results are primarily descriptive, with between-group comparisons performed as appropriate. De-identified individual case information may be disclosed.

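### The one laboratory safety comparison named is a crude abnormality rate, which hardly registers within-range shifts and is not limited to abnormalities arising after baseline (minor; cheap to improve)

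*Protocol article*

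**What the plan says.** - Section 2.10 (Statistical methods), on the laboratory panel: "Safety parameters (CBC, ALT, AST, urea, creatinine) are analyzed similarly, comparing abnormality rates".
- Section 2.9 (Safety evaluation) lists among the safety endpoints "and laboratory abnormalities (CBC, liver and renal function" and sets the status of the analysis: "Results are primarily descriptive, with between-group comparisons performed as appropriate".
- Section 2.7.4 (Safety assessments) gives panel and timing: "Safety evaluations include complete blood count, liver function (ALT, AST), and renal function (urea, creatinine). Assessment at baseline and Week 2".
- Table 1 in section 2.6.5 has a row "ALT, AST, BUN, Cr (liver and renal function"). As extracted it carries one mark, which reads as Week 2, and the table has no row for blood counts.
- The list of variables in section 2.10 for the linear mixed model contains no safety laboratory value. Categorical outcomes go to a chi-square or Fisher test.
- Section 2.3.4 (Exclusion criteria) does not exclude an abnormal liver or renal value as such. Hepatic and systemic disease appear there as causes of diarrhoea: "Acute or chronic diarrhea attributable to confirmed gastrointestinal pathology or systemic disease".

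**The concern.** An abnormal/normal rate discards everything about a laboratory value except the side of the reference limit on which it falls. If most of one arm's creatinine or ALT values rise but stay in range, the comparison shows almost nothing.

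The rate also mixes two groups: participants already abnormal at entry, who say little about the intervention, and those who became abnormal on treatment. Ages 18 to 80 and BMI up to 40 are admitted, so some abnormal baseline values are likely, although the documents give no figure.

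Renal markers matter here because the background-therapy section anticipates severe diarrhoea, described by "bowel motions per day with clinical signs of dehydration", and urea and creatinine are the laboratory values that bear most directly on dehydration. At stake is how informative the pilot's laboratory safety summary will be for the later trial it is meant to inform.

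**Working it through.** **1. The plan's own figure.** Section 2.4 gives 25 evaluable per group and 48 degrees of freedom. 30 × 0.85 = 25.5, taken as 25, and 25 + 25 − 2 = 48. This reproduces. No figure is stated for the laboratory comparison, so all laboratory inputs below are assumptions.

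**2. Shift within the reference range.** Assumed: log-normal creatinine, typical value (geometric mean) 75 µmol/L, log-SD 0.2, upper limit 104 µmol/L, baseline correlation 0.8, 25 per arm.

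- Abnormal rate with no rise: z = ln(104/75)/0.2 = 0.327/0.2 = 1.63, so about 5%.
- With a 10% rise: z = (0.327 − 0.095)/0.2 = 1.16, so about 12%.
- Standard error of the baseline-adjusted log difference: 0.2 × √(1 − 0.8²) × √(2/25) = 0.2 × 0.6 × 0.283 = 0.034. The 10% rise is then 0.095/0.034 = 2.8 standard errors.

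Simulated rejection rates at two-sided 0.05 (Fisher test on the rate; analysis of covariance on log values):

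| Rise in one arm | Abnormality rate | Baseline-adjusted log values |
|---|---|---|
| none | 0.1% | 5% |
| 10% | 3% | 77% |
| 20% | about 30% | over 99% |

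For the 10% rise, correlations of 0.5, 0.7 and 0.9 give about 47%, 64% and 96% for adjusted log values. The rate stays near 3% throughout.

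A second illustration drops the creatinine inputs. Put the limit at the 97.5th percentile and shift one arm's mean:

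| Shift (SD) | Abnormal rates | Power, rate | Power, unadjusted means |
|---|---|---|---|
| 0.3 | 2.5% v 4.8% | 0.001 | 0.18 |
| 0.5 | 2.5% v 7.2% | 0.005 | 0.42 |
| 0.8 | 2.5% v 12.3% | 0.05 | 0.81 |

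**3. Pre-existing abnormalities.** Assumed: prevalence b equal in expectation in both arms and persisting; new abnormalities in 2% v 20% of those normal at baseline. The crude rate in an arm is b + (1 − b) × new rate. At b = 20% this is 0.2 + 0.8 × 0.02 = 21.6% against 0.2 + 0.8 × 0.20 = 36%.

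| Prevalence b | Power, crude rate | Chance of baseline imbalance ≥ 3 participants |
|---|---|---|
| 0% | 0.30 | 0 |
| 5% | 0.26 | 0.10 |
| 10% | 0.19 | 0.23 |
| 20% | 0.12 | 0.37 |
| 30% | 0.10 | 0.44 |

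With 2% new abnormalities in both arms, the Fisher type I error is 0.000 to 0.024 over this range, never above 0.05. Part of the power loss comes from having fewer participants at risk. At b = 20%, comparing only the 25 × 0.8 = 20 per arm who were normal at baseline gives exact Fisher power 0.27, against 0.12 for the crude rate.

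**4. Is the baseline value available?** Section 2.7.4 places the whole panel at baseline and Week 2. Table 1, as extracted, marks the liver and renal row once and omits blood counts. If Table 1 governed, neither a baseline-adjusted summary nor a count of new abnormalities could be produced.

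**The case against.** **Ambiguous wording.** The article does not say that rates are the sole analysis. *Similarly* may carry over methods given earlier in section 2.10, which include t-tests and Mann–Whitney tests for continuous variables, though in the paragraph on baseline characteristics. This stands: a reader might infer that laboratory values are compared only as rates, and the text does not settle that. The rate is simply the one comparison named.

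**Detail left elsewhere.** Shift tables and definitions of new abnormality usually sit in an analysis plan or full protocol, neither of which is shown, and section 2.6.5 refers part of the sampling schedule to an appendix. Their absence is no fault. What remains is that the article does name a measure, and that measure is a poor one at this sample size.

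**Randomization.** A reader might infer that abnormalities present before treatment would be reported as treatment differences. With 1:1 allocation they are equal in expectation and the type I error is not inflated, so that reading fails. Dilution and chance imbalance remain.

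**Descriptive pilot.** The trial is not sized for efficacy testing and safety is mainly descriptive, so detection rates are only a gauge of information lost. That limits the weight of the point. A descriptive abnormality rate nevertheless hides a within-range shift just as a tested one does.

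**Other safety data.** It is tempting to treat urea and creatinine as the only window on dehydration. They are not: adverse events, daily stool records and home symptom logs are also collected.

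**Conclusion.** The point holds as a minor one. The article names the abnormality rate as its laboratory safety comparison, leaves *similarly* unresolved, and does not confine the rate to abnormalities arising after baseline. At about 25 per arm the rate carries little information on within-range shifts: about 3% against 77% detection of a 10% creatinine rise, the latter 47% to 96% across correlations of 0.5 to 0.9. Pre-existing abnormalities weaken a true signal (power 0.30 falling to 0.12 at 20% prevalence, in the assumed scenario) without biasing the comparison. All laboratory levels, spreads, limits, correlations and prevalences are assumptions, and the position of the mark in Table 1 is read from extracted text. The documents do not support the stronger conclusion that the trial's safety findings would be unreliable.

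**What to change.** Replace the laboratory sentence in section 2.10 with wording to this effect:

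1. ALT, AST, urea, creatinine and blood counts are summarised by arm as baseline-adjusted Week 2 values, on the log scale where skewed, with the between-arm contrast and 95% CI.
2. Abnormalities are shown as a baseline-to-Week 2 shift table, with new abnormalities (normal at baseline, abnormal at Week 2) given by arm.
3. Both are descriptive, and the crude abnormality rate is kept as a supplementary listing.

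Reconcile section 2.7.4 with Table 1 on the timing of the liver and renal tests and on the missing row for blood counts, since both summaries need the baseline sample.

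Cost: one or two sentences and a few table rows. If the schedule in section 2.7.4 stands, no additional sampling is needed; if Table 1 reflects what is done, the baseline draw has to be settled first.
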